### Concealment mechanism {16b}

In this study, the allocation sequence was implemented using a centralized, computer-generated randomization process. This process will be managed by a dedicated statistician who will not be involved in participant recruitment or intervention delivery, thereby ensuring concealment of the sequence until interventions are assigned.

Once the general practices have been recruited, demographic and practice characteristics (including the preferred language of patients, urban or rural location, and demographic characteristics of the general practitioners) will be collected and entered into randomization software. The software then generates a random allocation sequence, assigning practices to either the intervention group (use of the ABCC tool) or the control group (usual care without the ABCC tool).

The allocation sequence will be kept confidential and will not be disclosed to the general practice or research team involved in the recruitment and follow-up of participants until the assignment point. This approach ensures that the assignment process is not influenced by any pre-existing knowledge or bias and that allocation concealment is maintained throughout the study.

Once the randomization process is completed, each general practitioner will be informed of their group assignment by the central research team and the necessary instructions or equipment (including the tablet PC for the intervention group) will be provided. This method ensured that the allocation process was transparent and unbiased, thereby maintaining the integrity of the study design.

### Implementation {16c}

Participant enrollment and group allocation will be managed directly by the research team. After generation of the random allocation sequence, practices will be notified of their assignment to either the intervention or control group. Necessary equipment, including a tablet PC loaded with the ABCC tool, along with instructions for use, will be provided to practices in the intervention group to ensure a clear and efficient setup for the conduct of the study.

## Assignment of interventions: blinding

### Who will be blinded {17a}

In this study, blinding of trial participants and care providers (i.e., general practitioners and practice nurses) is not possible because of the nature of the intervention, as they will know whether they are using the ABCC tool or delivering standard care.

However, outcome assessors and data analysts will be blinded to the assignment of the interventions. This is achieved by coding the groups in the dataset in a manner that does not reveal their assignments (using non-descriptive labels, Groups A and B). The individual who assigns these codes maintains a separate, secure record of the code that corresponds to the treatment group.

This record will not be shared with outcome assessors and data analysts. The outcome assessors, who will evaluate the results of the patients’ self-reported outcomes, and the data analysts, who will perform statistical analyses of the collected data, will be blinded to the allocation.

### Procedure for unblinding if needed {17b}

In this study, only the outcome assessors and data analysts are blinded. Because the trial participants and care providers are not blinded, there is no need for unblinding procedures in these groups.

For outcome assessors and data analysts, unblinding may be permissible under specific circumstances such as serious adverse events that require immediate knowledge of the participant’s intervention group to ensure appropriate medical care. Although the need for unblinding may be relatively low due to the nature of the intervention (ABCC tool versus standard care), having an established unblinding procedure in place ensures that any unforeseen circumstances can be managed appropriately without compromising the overall study design. An independent designated person will be identified as responsible for managing the unblinding process, ensuring that it occurs only when the documentation of any unblinding event is justified and maintained. Each designated person evaluates each request for unblinding. If the request is approved, the designated person will access the secure record with the group allocation codes and disclose the participant’s intervention group only to relevant individuals who require information to manage the situation.

## Data collection and management

### Plans for assessment and collection of outcomes {18a}

The assessment and collection of outcomes will be performed by using well-established survey instruments. These include the Patient Assessment of Chronic Illness Care (PACIC) as the primary outcome, that is, perceived quality of care. Secondary outcomes such as health-related quality of life, patient activation, and capability well-being will be assessed using EQ-5D-5L and Patient Activation Measure (PAM), respectively. Data collection will follow a set schedule with checkpoints at 6-, 12-, and 18-month intervals from the start of the intervention to monitor changes in these outcomes over time.

The research team will facilitate survey completion through telephone or email contact, offering participants the option to complete surveys online or on paper. In addition, participants visiting their primary care physician’s office will have the option of using the ABCC tablet to complete the survey during their visit.

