## Assignment of interventions: allocation

### Sequence generation {16a}

In this cluster-randomized trial, general practices throughout South Tyrol serve as the unit of randomization. After recruitment, these practices will be assigned to either the intervention or control group through a stratified randomization process. Stratification factors include the patients’ preferred language (Italian or German), the location of the practice (urban or rural), and the demographic characteristics of the general practitioners (sex and age). Sequences will be generated using computer software to pre-generate random assignments. Practices in the intervention group will use the ABCC tool via a provided tablet PC, while those in the control group will continue their usual care without access to the tool.

To maintain the integrity of this randomization process and control for potential confounding, these stratifying variables will be explicitly included in the analytical models.

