## Statistical methods

### Statistical methods for primary and secondary outcomes {20a}

The data evaluation process is based on the intention-to-treat principle. Initial analyses will be performed on the entire group of patients with COPD, asthma, type 2 diabetes, and heart failure, which also includes those with multiple conditions. Subsequently, the impact of the ABCC tool is examined separately for patients with COPD, asthma, type 2 diabetes, and heart failure, irrespective of the presence of coexisting conditions.

Considering the clustered design of the study, a three-level multilevel analysis will be conducted: general practice, patient, and measurement. The study will apply linear mixed models to analyze outcomes to account for the grouping of measurements within patients in general practice. Fixed factors will include “treatment group,” “time” (categorical), and “interaction between treatment group and time.”

Given that randomization of patients into the intervention or control groups is not feasible, factors believed or known to influence the perceived quality of care and/or the use of the ABCC tool will be regarded as potential confounders. The intervention or control group assignment hinges on the accessibility of the ABCC tool (i.e., the presence of the ABCC tool tablet PC in general practice). Potential confounders include ethnic background (native/Western foreigner/non-Western foreigners), multimorbidity (yes/no), educational status (low/middle/high), age (continuous in years), sex (male/female), body mass index (BMI, kg/m2, continuous), smoking habits (never/former/current), location of the general practice (urban/rural), year of the general practitioner’s graduation (less/more than 10 years ago), and general practice in a group setting (yes/no).

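### Outcome questionnaires may be answered at the GP's office on the ABCC tablet, a device the protocol gives only to intervention practices, so the routes available for the unblinded primary outcome differ by arm

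*Protocol article*

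**What the plan says.** **Collection of outcomes.** Protocol article, Plans for assessment and collection of outcomes {18a}: the research team contacts participants by telephone or email, "offering participants the option to complete surveys online or on paper". In addition, participants visiting their GP "will have the option of using the ABCC tablet to complete the survey during their visit". The tablet option is not restricted to one arm. The instruments are the PACIC (primary), the EQ-5D-5L and the PAM.

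**Who holds the tablet.**
- Sequence generation {16a}, on intervention practices: "Practices in the intervention group will use the ABCC tool via a provided tablet PC". On control practices, the same section states that "those in the control group will continue their usual care without access to the tool".
- Concealment mechanism {16b}: practices receive instructions or equipment after assignment, "including the tablet PC for the intervention group".
- Implementation {16c}: equipment for intervention practices, "including a tablet PC loaded with the ABCC tool".
- Statistical methods for primary and secondary outcomes {20a}: group assignment depends on access to the tool, explained as "the presence of the ABCC tool tablet PC in general practice".

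**Blinding.** Who will be blinded {17a}: patients and care providers are not blinded; "outcome assessors and data analysts will be blinded to the assignment of the interventions". The same section describes the outcomes as self-reported by patients.

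**The concern.** The PACIC is the patient's own rating of the care received, given by someone who knows the allocation. If one arm can give that rating inside the practice being rated, on the device that carries the intervention, any effect of place or device on the answers becomes part of the estimated treatment effect. The Discussion has GPs reviewing the tool's results with patients during the consultation. Follow-up assessments and visits also uses these contacts to check that intervention patients use the tool correctly. Outcome measurement could therefore sit close to delivery of the intervention in one arm.

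Two mechanisms are at stake. Answers may shift with mode or place, for example through courtesy to the practice or the recency of a visit. Completeness may also differ, because one arm has an additional convenient way to respond.

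A later analysis cannot cleanly repair this. A mode that occurs in only one arm cannot be separated from treatment by comparing arms. Within the intervention arm, tablet users are self-selected, so comparing them with non-users does not isolate the mode effect either. It has to be settled by design.

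**Working it through.** **1. Sections set side by side.** {18a} offers the tablet to participants visiting their GP, without restriction by arm. {16a}, {16b}, {16c} and {20a} put the tablet in intervention practices. No section supplies a tablet or another survey device to control practices, or requires the same mode in both arms. Two readings remain:
- (a) {18a} can operate only where a tablet exists, so only intervention patients have the in-practice, on-device route.
- (b) {18a} means what it says for everyone, so control practices hold a tablet carrying the tool. That contradicts the four other sections and opens a path to the contamination that randomization by practice was meant to prevent (Trial design {8}).

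Under either reading the text needs correcting.

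**2. The plan's own sample size.** Inputs from Sample size {14}: difference 0.49, SD 0.96, effect size 0.51, two-sided alpha 0.05, power 90%, ICC 0.05, 10 patients per practice, division by 0.9 for variable cluster size and by 0.75 for dropout.
- Two-sample t-test: 81.8, rounded up to 82 per group (agrees).
- Design effect: 1 + (10 − 1) × 0.05 = 1.45 (agrees).
- 82 × 1.45 / 0.9 / 0.75 = 176.1, rounded up to 177 (agrees). The plan recruits 180 per group.

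The sample size is not in question here. It supplies the precision for the next step.

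**3. Standard error implied by the plan.**
- Effective n per arm = 180 × 0.75 × 0.9 / 1.45 = 83.8.
- SE of the difference = 0.96 × √(2 / 83.8) = 0.148 PACIC points.

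**4. Illustrative bias under reading (a).** The protocol gives neither uptake nor a mode effect, so both are assumptions. With baseline not taken on the tablet:
- bias = (share of intervention patients answering on the tablet) × (shift in PACIC points);
- type I error = 1 − Φ(1.96 − bias/SE) + Φ(−1.96 − bias/SE).

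| Uptake | Shift | Bias | % of 0.49 | Type I error |
|---|---|---|---|---|
| 10% | 0.1 | 0.01 | 2.0 | 5.1% |
| 10% | 0.3 | 0.03 | 6.1 | 5.5% |
| 25% | 0.2 | 0.05 | 10.2 | 6.3% |
| 50% | 0.1 | 0.05 | 10.2 | 6.3% |
| 50% | 0.2 | 0.10 | 20.4 | 10.3% |
| 50% | 0.3 | 0.15 | 30.6 | 17.3% |

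**5. Effect of baseline mode.** The outcome is change over 18 months, and the model contains group, time and their interaction. Patients are enrolled after practices are randomized (Enrollment and baseline assessment), so a tablet could already be in the practice at baseline. If shares p0 at baseline and p1 at follow-up use it with the same shift, the bias in change is (p1 − p0) × shift, which is zero when p1 = p0. The protocol does not fix the baseline mode, so the table shows the case without cancellation.

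**The case against.** The strongest defence is that the tablet is optional and that online and paper forms are open to both arms. Only the available route differs for certain, and actual use may be small. This stands, and it is why no single bias figure can be given. It does not remove the asymmetry: self-selected use in one arm is still use in one arm.

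A second defence is that an unseen analysis plan or data management plan may record mode and adjust for it. Recording may well be covered there. Adjustment would not solve the problem, for the reason given above.

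A reader might also infer more than the protocol supports:
- *That controls answer at home or by phone.* {18a} names telephone and email as contact routes and online or paper as completion modes. It does not say where forms are filled in. Both arms have follow-up visits, so a control patient could complete a paper form in the practice.
- *That the bias is a sizeable fraction of the target difference.* That needs high uptake, a clear shift and no cancellation through baseline. At the low end the effect is negligible.
- *That both mechanisms favour the tool.* A courtesy effect would plausibly raise scores, but better response in one arm has no fixed direction. Retaining less satisfied patients could lower that arm's mean.
- *That the blinding statement is false or conceals something.* {17a} says openly that patients are unblinded and that assessors evaluate self-reported results, and the Discussion acknowledges subjective outcomes. The narrower point is that blinded assessors and analysts do not protect a score that the unblinded patient has already given.

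**Conclusion.** The concern holds as an inconsistency between {18a} and sections {16a}, {16b}, {16c} and {20a}, with a consequence for how the primary outcome is measured. As written, either the available mode and place of PACIC completion differ by arm, or control practices hold the intervention device against the protocol's own description.

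The size is not known. On the plan's own precision (SE about 0.148), the illustrated bias runs from 0.01 PACIC points (type I error about 5.1%) to 0.15 points (about 17%). These figures assume uptake of 10% to 50%, a shift of 0.1 to 0.3 points and no tablet use at baseline; with tablet use at baseline they shrink. An upward direction is plausible, not demonstrated. The point is worth correcting because the remedy is simple and removes a rival explanation for a positive result. The documents do not show that the trial's result would be materially biased.

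**What to change.** - In {18a}, remove the ABCC-tablet option for the PACIC, EQ-5D-5L and PAM.
- State that both arms use the same routes at baseline, 6, 12 and 18 months: online or paper, with reminders from the research team, as {18a} already provides.
- Record the mode of completion at each assessment.
- If in-practice completion is wanted for retention, an alternative is a neutral survey device without the tool in all practices of both arms, at extra equipment cost.

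**Cost.** The first three items are mainly a wording change, and Trial status reports that recruitment had not begun. The downside is real: intervention patients who would have answered on the tablet, possibly more than a few, need a reminder to answer online or on paper. With 25% dropout already expected, that follow-up effort should be planned.

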### Plans to promote participant retention and complete follow-up {18b}

Retention of participants and ensuring complete follow-up will be achieved by employing various strategies [27]. We will maintain regular communication with the participants, provide them with feedback about the progress of the study, and recognize their contributions to the research. Furthermore, the data collection schedule was designed to minimize participant burden, and we will accommodate participants’ needs wherever possible to encourage continued involvement.

### Data management {19}

A robust data management plan is in place to store, organize, and access the collected data. We will use a secure, centralized data management system for these purposes, and only authorized study personnel will have access to it [28]. In addition, regular data audits will be conducted to identify and correct any data entry errors or inconsistencies, thereby ensuring data integrity.

### Confidentiality {27}

To protect participants’ confidentiality, all personal identifying information is separated from the study data and replaced with unique study identifiers. Access to personal information is limited to the essential personnel. All data will be stored securely in compliance with data protection regulations, and any report or publication will contain only aggregated data, with no possibility of identifying individual participants. After the trial has ended, all personal identifying information will be securely destroyed, and anonymized study data will be preserved for a predefined period as per regulatory guidelines, ensuring ongoing confidentiality.

## Statistical methods

### Statistical methods for primary and secondary outcomes {20a}

The data evaluation process is based on the intention-to-treat principle. Initial analyses will be performed on the entire group of patients with COPD, asthma, type 2 diabetes, and heart failure, which also includes those with multiple conditions. Subsequently, the impact of the ABCC tool is examined separately for patients with COPD, asthma, type 2 diabetes, and heart failure, irrespective of the presence of coexisting conditions.

Considering the clustered design of the study, a three-level multilevel analysis will be conducted: general practice, patient, and measurement. The study will apply linear mixed models to analyze outcomes to account for the grouping of measurements within patients in general practice. Fixed factors will include “treatment group,” “time” (categorical), and “interaction between treatment group and time.”

Given that randomization of patients into the intervention or control groups is not feasible, factors believed or known to influence the perceived quality of care and/or the use of the ABCC tool will be regarded as potential confounders. The intervention or control group assignment hinges on the accessibility of the ABCC tool (i.e., the presence of the ABCC tool tablet PC in general practice). Potential confounders include ethnic background (native/Western foreigner/non-Western foreigners), multimorbidity (yes/no), educational status (low/middle/high), age (continuous in years), sex (male/female), body mass index (BMI, kg/m2, continuous), smoking habits (never/former/current), location of the general practice (urban/rural), year of the general practitioner’s graduation (less/more than 10 years ago), and general practice in a group setting (yes/no).

Each potential confounder will be independently added to the aforementioned linear mixed model, and if it is significantly associated with the outcome (*p* ≤ 0.05), it will be considered a confounder. Both unadjusted and adjusted treatment effects will be reported along with their corresponding 95% confidence intervals and *p*-values. Statistical significance is set at *p* < 0.05. To account for multiple potential confounders, inverse probability of treatment weighting using propensity scores will be used as a sensitivity analysis. The use of hierarchical modeling aims to methodically evaluate the significance of confounders, prioritizing them by their theoretical relevance and observed impact on study outcomes. To ensure analytical robustness, R-squared values will further quantify each covariate’s contribution to the model.

The primary outcome will encompass all measurement times, including data collected at 6, 12, and 18 months. The analytic strategy will use longitudinal data collected at 6, 12, and 18 months, incorporating random effects models to account for the nesting of patients within practices. Model comparison techniques will be used to assess the fit of increasingly complex models to ensure that the analysis captures the impact of the intervention while accounting for provider variability within practices.

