### Methods for additional analyses (e.g., subgroup analyses) {20b}

In addition to the secondary objective of assessing the shift in perceived quality of care, employing the PACIC against regular care after 18 months, individually for each chronic condition, further subgroup analyses will be conducted based on age, sex, multimorbidity status, and educational level, as these factors could potentially influence perceived quality of care and the use of the ABCC tool.

Linear mixed models are used for these analyses, with the subgroups added as interaction terms to assess whether the effect of the intervention varied across different subgroups. The subgroup analyses are specified a priori in the study protocol to avoid data dredging.

Adjusted analyses will also be conducted to control for potential confounders. Factors known or hypothesized to be associated with perceived quality of care or the use of the ABCC tool will be considered potential confounders and adjusted for in the analysis, including national background, location of general practice, year of graduation of the general practitioner, and whether the general practice is part of a group.

For adjusted analyses, especially when significant confounders are identified, the Inverse Probability of Treatment Weighting method will be used as described by Hernán et al. [29]. This approach, designed to balance the distribution of observed baseline covariates across treatment groups, mitigates potential bias and is fundamental to estimating the causal effects of interventions.

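### The promised stratification factors are missing from the specified model, covariates enter by outcome p-value, and neither the primary estimate nor the role of IPTW is fixed

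*Protocol article*

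**What the plan says.** All references are to the protocol article.

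- **Sequence generation {16a}.** The design is cluster-randomised: "general practices throughout South Tyrol serve as the unit of randomization". On strata it says "Stratification factors include the patients’ preferred language (Italian or German), the location of the practice (urban or rural"), and the sentence goes on to GP sex and GP age. It then commits that "these stratifying variables will be explicitly included in the analytical models".
- **Statistical methods {20a}, model.** A three-level linear mixed model (practice, patient, measurement) with fixed effects for treatment, categorical time and their interaction. No stratification factor is named.
- **Statistical methods {20a}, confounders.** Adjustment is introduced with "Given that randomization of patients into the intervention or control groups is not feasible", and group assignment is described as turning on whether the practice has the tool. Ten candidates follow: ethnic background, multimorbidity, education, age, sex, BMI, smoking, practice location, GP graduation year and group practice.
- **Statistical methods {20a}, selection.** "Each potential confounder will be independently added to the aforementioned linear mixed model, and if it is significantly associated with the outcome" at p ≤ 0.05, it is treated as a confounder. Unadjusted and adjusted effects are both reported, with confidence intervals and p-values. Neither is named as primary.
- **IPTW.** In {20a}, "inverse probability of treatment weighting using propensity scores will be used as a sensitivity analysis". In {20b}, "For adjusted analyses, especially when significant confounders are identified, the Inverse Probability of Treatment Weighting method will be used".
- **Additional analyses {20b}.** National background, practice location, GP graduation year and group practice are to be adjusted for. No p-value condition is repeated.

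**The concern.** The sections give three different rules for what enters the model: the strata unconditionally ({16a}), candidates one at a time by outcome p-value ({20a}), and a named list without a screen ({20b}). An analysis plan cannot follow all three.

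The {20a} rule is also weak in itself. A covariate confounds the treatment comparison only if it is related to the outcome and also differs between arms. The screen tests the first condition and ignores the second. It lets the trial's own outcome data decide the adjusted model, so that model is unknown until the data are in.

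The strata raise a separate issue. Stratified randomisation balances the arms on the strata. If the strata predict the outcome and the model leaves them out, the standard error is too large for the design, so the test is conservative and power is lost.

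Finally, the effect estimate that answers the primary question is not settled while unadjusted, screened-adjusted and possibly weighted results stand side by side.

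**Working it through.** **1. The plan's own figure, for context.** With d = 0.49/0.96 = 0.51, two-sided α = 0.05 and 90% power, the t-test needs 81.6, so 82 per group. The design effect is 1 + (10 − 1) × 0.05 = 1.45. Then 82 × 1.45 / 0.9 / 0.75 = 176.1, so 177 per group. This matches {14}. The present point does not change it.

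**2. Strata set against the {20a} model.**

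| Stratification factor ({16a}) | In the fixed effects of {20a}? | Among the ten candidates? |
|---|---|---|
| Patient language | no | no |
| Practice location | no | yes, subject to p ≤ 0.05 |
| GP sex | no | no (the listed sex sits among patient characteristics) |
| GP age | no | no (graduation year, under or over 10 years, is at most a proxy) |

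Named in {16a}: 4. Candidates in {20a}: 1. Guaranteed by {20a}: 0.

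**3. How far the screen depends on the data.** If all ten candidates were unrelated to the outcome and independent (an assumption), the chance that at least one passes is 1 − 0.95^10 = 0.40. In a separate null simulation (3,000 replicates, 36 practices of 5–10 patients, ICC 0.05, 13 covariate degrees of freedom with modest effects), between 1 and 5 covariates passed (5th to 95th percentile). The type I error of the screened-adjusted analysis was 5.4%, against 5.5% unadjusted. The screen makes the model unpredictable, but it did not inflate the error rate.

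**4. The effect of omitting the strata.** The protocol does not say how prognostic they are, so a range is shown.

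Assumptions: SD 0.96 and ICC 0.05 from {14}; 36 practices; 10 × 0.75 = 7.5 patients per practice after dropout; four binary strata of equal strength; alternating allocation within strata; analysis of practice means; 4,000 replicates.

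- Between-practice variance: 0.05 × 0.9216 = 0.0461.
- Within-practice part of a practice mean: 0.95 × 0.9216 / 7.5 = 0.1167.
- Total: 0.1628. Practice-level strata can explain at most 0.0461 / 0.1628 = 0.28 of it.

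| Share of practice-mean variance explained by strata | Type I error: none / location only if p ≤ 0.05 / all four | Power at a difference of 0.3: same order |
|---|---|---|
| 0 | 0.054 / 0.055 / 0.055 | 0.58 / 0.59 / 0.57 |
| 0.1 | 0.045 / 0.046 / 0.050 | 0.59 / 0.59 / 0.61 |
| 0.3 (just above the 0.28 ceiling) | 0.025 / 0.030 / 0.051 | 0.58 / 0.61 / 0.71 |

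Monte Carlo standard errors are about 0.003 for type I error, from √(0.05 × 0.95/4000), and 0.008 for power, from √(0.58 × 0.42/4000).

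The difference of 0.3 is illustrative and smaller than the planned 0.49. The standard error of the arm difference is √(2 × 0.1628/18) = 0.1345. So 0.3 gives a noncentrality of 2.23 and, by the noncentral t on 34 degrees of freedom, power 0.58, which agrees with the table. The planned 0.49 gives 3.64 and power 0.94 under the same assumptions. There is little power left to gain if the planned effect is true; the loss matters mainly for smaller effects.

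**The case against.** Several points on the other side stand.

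- **Patient-level adjustment has a real purpose here.** Patients are enrolled by healthcare providers after practices are allocated (study setting {9}, participant timeline {13}), and providers are not blinded ({17a}). Differential recruitment can therefore unbalance the arms. As an illustration, take two measured covariates with effect 0.25 each, shifted by 0.2 SD between arms. The unadjusted bias is 2 × 0.25 × 0.2 = 0.10, with simulated type I error 8.1%. The screened-adjusted and practice-clustered IPTW analyses each reduced the bias to about 0.01 (4.8% and 5.0%). It would be wrong to say that IPTW can remove no bias in this trial. This argues for a fixed list of patient covariates. It does not argue for a p-value screen, and it is not the reason {20a} gives.
- **The sentence on feasibility is literally true of patients.** What misleads is that it is offered as the ground for confounder control without saying that practices are randomised.
- **{16a} is an explicit commitment, and the lists in {20a} are worded as inclusions.** A sympathetic analyst could add the strata. But the screen in {20a} then contradicts {16a} for location, the one factor that both mention.
- **An article may leave the choice of primary model to the analysis plan.** That is fair for the omission alone. It does not excuse conflicting statements that the analysis plan would have to overrule.
- **IPTW in {20b} sits under additional analyses** and may be meant as the same sensitivity analysis. The wording does not say so.

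A reader might also take "Model comparison techniques will be used to assess the fit of increasingly complex models" and the use of R-squared as further covariate selection. The text ties the former to random effects and provider variability within practices, and describes the latter as quantifying contributions.

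**Conclusion.** The point holds as an inconsistency and a weak covariate rule, to be corrected before data exist. The model in {20a} does not deliver the strata promised in {16a}. Selection by outcome p-value does not identify confounding and leaves the adjusted model unknown in advance. The primary estimate and the role of IPTW are not fixed.

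The size depends on how prognostic the strata are, which the protocol does not state. Under the assumptions above the cost of omitting them runs from nothing, through 0.59 against 0.61 power at a share of 0.1, to type I error 0.025 and power 0.58 against 0.71 near the ceiling. The direction is conservative.

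Stronger readings are tempting but not supported:

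- *The false positive rate is inflated.* The screen alone gave 5.4% against 5.5%. Rates of 6.7% (either of two analyses significant) or 8.2% (any of three) need a rule that any significant analysis counts, which the protocol does not state. A rate of 8.0% for IPTW needs standard errors that ignore practice, which it does not specify; with clustered errors the rate was 4.8%.
- *The primary estimate is picked after seeing outcomes.* The protocol reports both estimates and selects neither.
- *The trial is analysed as if non-randomised.* Intention-to-treat, a practice level in the model and an unadjusted effect are all specified.

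**What to change.** 1. In {20a}, delete the p ≤ 0.05 screen.
2. Name one primary model: a linear mixed model with practice and patient random effects; treatment, time and treatment × time; the factors actually used to stratify randomisation; and a short fixed list of patient baseline covariates from the existing ten, for example age, sex and multimorbidity. Keep all of them whatever their p-values. The patient covariates belong in the primary model and should not be optional, because practice-level strata cannot correct differential patient recruitment.
3. Report the unadjusted effect as secondary.
4. Reword the rationale in {20a}: practices are randomised, and patient-level adjustment addresses possible differential recruitment after allocation by unblinded providers.
5. Give IPTW one role, a sensitivity analysis with practice-clustered errors, and align {20b} with it. Align the {20b} adjustment list with the fixed list.

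**Cost.** Wording only; the trial status section says recruitment had not begun. The sample size is unchanged. The price is a few practice-level degrees of freedom. Four binary strata take 36 − 2 = 34 to 36 − 6 = 30, which moves the two-sided 5% critical value from 2.03 to 2.04. If GP age is dichotomised (an assumption), full crossing gives 2^4 = 16 cells for 36 practices, about 2.25 each, so the factors should enter as main effects.
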